### Measurements

2.10

Data collection will be performed by blinded researchers independent of the recruitment process. Prior to the commencement of testing, all assessment personnel will undergo uniform standardized training to ensure the consistency and reliability of measurements. To guarantee strict adherence to the study protocol, participants will be provided with detailed information regarding the operating procedures, research objectives, and specific requirements before any measurements are taken. Assessments will be scheduled at baseline and at week 12 (post-intervention). The primary outcome will be FMD. Secondary outcomes will include cardiovascular function, glucose and lipid metabolism, circulating biomarkers of inflammation and oxidative stress, and *ex vivo* functional assays using participant-derived serum, including serum transfer experiments using HUVECs and molecular profiling of EPCs cultured in the presence of the participants’ serum. With the exception of the OGTT and the 2-h PPG test, all assessments will be conducted following a 12-h overnight fast. Subjects will be requested to avoid strenuous physical activity and abstain from caffeine and alcohol for 24 hours prior to evaluation. They will also be required to wear loose-fitting clothing. On the morning of the assessment, routine medications will be withheld to eliminate potential pharmacological interference. In order to eliminate the acute biological effects of a single exercise bout, we will schedule post-intervention tests after a two-day rest period (48 hours) following the last session. Furthermore, to avoid reactive hyperglycemia induced by prolonged fasting, venous blood sampling will be uniformly performed the morning following an overnight fast.

### Blood collection and preparation

2.11

Following a 12-h overnight fast, approximately 8 mL of peripheral venous blood will be collected from participants via median cubital venipuncture. Blood samples will be distributed into EDTA-anticoagulated tubes for the measurement of glycated hemoglobin (HbA1c) and the isolation of PBMCs, and into serum collection tubes for serum preparation. Serum will be used for routine biochemical analyses (glucose and lipids), insulin measurement, assessment of circulating inflammatory and oxidative stress biomarkers, as well as for serum transfer experiments and the establishment of a human serum culture system for EPCs. After clotting at room temperature for 30 min, samples in serum collection tubes will be centrifuged at 3,000 × g for 15 min at 4 °C. The resulting serum will be collected under sterile conditions, filtered through a 0.22 μm syringe filter for cell culture applications, aliquoted to avoid repeated freeze–thaw cycles, and stored at −80 °C until analysis.

### Primary outcome

2.12

#### Vascular endothelial function

2.12.1

Vascular endothelial function will be assessed via flow-mediated dilation (FMD). Measurements will be conducted by professionally trained researchers utilizing an ultrasound vascular imaging unit (UNEXEF18G; UNEX, Japan). Measurement procedures will follow our previously published paper (21). The formula for FMD is as follows:

$$\text{FMD}\%=\frac{\text{peak post}-\text{hyperemic diameter }-\text{ baseline arterial diameter}}{\text{baseline arterial diameter}}\times 100\%.$$

### Secondary outcomes

2.13

#### Glucose metabolism

2.13.1

Glucose metabolism parameters will include fasting blood glucose (FBG), glucose levels during a standard 75-g oral glucose tolerance test (OGTT), 2-h postprandial glucose (2-h PPG), and glycated hemoglobin (HbA1c). An automated biochemical analysis system equipped with standardized enzymatic assays will be utilized to determine plasma glucose concentrations (FBG, 2-h PPG, and 2-h OGTT). Meanwhile, high-performance liquid chromatography (HPLC) will be employed for the quantification of HbA1c. Measurement procedures will follow our previously published paper (21).

#### Insulin level

2.13.2

Fasting insulin levels will be determined using enzyme-linked immunosorbent assay (ELISA) kits. Subsequently, the Homeostatic Model Assessment of Insulin Resistance (HOMA-IR) index will be calculated in conjunction with FBG values to evaluate insulin sensitivity. The formula for HOMA-IR is as follows:

HOMA-IR=Fasting blood glucose (mmol/L)×Fasting insulin (µU/mL)/22.5

#### Lipid metabolism

2.13.3

Lipid metabolism parameters will include total cholesterol (TC), triglycerides (TG), high-density lipoprotein cholesterol (HDL-C), and low-density lipoprotein cholesterol (LDL-C). Plasma concentrations of these lipids will be determined using an automated biochemical analyzer with the corresponding commercial kits.

#### Cardiovascular risk factors

2.13.4

Body weight, standing height, hip circumference (HC), and waist circumference (WC) will be measured using a digital scale, a stadiometer, and a non-elastic tape measure, respectively. Body mass index (BMI) will be computed as 
body weight (kg)/height squared (m^2^), whereas the waist-to-hip ratio (WHR) will be determined as 
WC (cm)/HC (cm). Body fat distribution will be evaluated through a combination of skinfold thickness testing and ultrasound scanning. Skinfold thickness will be measured at the triceps, abdomen, and subscapular sites using a skinfold caliper, with readings recorded to the nearest 1 mm. Ultrasound scanning will be performed using a calibrated analyzer (BodyMetrix BX-2000; IntelaMetrix, USA) at the following seven sites: midaxillary, subscapular, triceps, abdomen, chest, suprailiac, and thigh. Measurement procedures will follow our previously published paper (21).

#### Arterial stiffness

2.13.5

Arterial stiffness will be assessed via brachial-ankle pulse wave velocity (baPWV). Measurements will be performed by professionally trained researchers using an automated arteriosclerosis screening device (BP-203RPE III; Omron, Japan). Measurement procedures will follow our previously published paper (21).

#### Blood pressure

2.13.6

Blood pressure (BP) will be measured by trained cardiologists using an automated blood pressure monitor (Omron HEM 3; Omron, Japan). Measurement procedures will follow our previously published paper (21).

#### Circulating oxidative stress biomarkers

2.13.7

To characterize systemic oxidative stress status at the circulating level, biomarkers will be assessed in serum samples. Serum levels of ROS will be assessed using a fluorescence-based assay kit. Serum malondialdehyde (MDA) levels will be determined using a thiobarbituric acid (TBA)-based colorimetric assay (TBARS method), and superoxide dismutase (SOD) activity will be measured using a WST-1–based colorimetric assay, both performed using commercially available microplate-based kits. Additionally, serum concentrations of nuclear factor erythroid 2–related factor 2 (Nrf2) will be quantified using ELISA kits following standard protocols.

#### Circulating inflammatory biomarkers

2.13.8

To reflect systemic inflammatory status at the circulating level, inflammatory biomarkers will be measured in serum samples. Serum levels of NLR family pyrin domain containing 3 (NLRP3), interleukin-1β (IL-1β), tumor necrosis factor-alpha (TNF-α), interleukin-6 (IL-6), high-sensitivity C-reactive protein (hs-CRP), and interleukin-10 (IL-10) will be quantified using ELISA kits following standard protocols.

#### HUVEC serum transfer experiment and cellular analyses

2.13.9

To investigate the regulatory effects of exercise-induced circulating factors on endothelial redox homeostasis and inflammation, serum transfer experiments will be conducted using individual serum samples obtained from all participants in both the AE and CON groups. To preserve individual biological variability, serum from each participant will be applied individually to cell cultures without pooling. Human umbilical vein endothelial cells (HUVECs; Servicebio, Cat# STCC12103P-1) will be cultured to 70%–80% confluency, followed by synchronization in low-serum medium (0.5%–1% FBS) for 4–6 h. The cells will then be incubated for 24–48 h in medium supplemented with 2% individual participant serum. After the incubation period, the cells will be harvested for subsequent functional and molecular assessments.

To evaluate cellular redox homeostasis and inflammatory responses, intracellular ROS levels will be determined using a fluorescent probe assay. The protein expression of key oxidative stress–related molecules—including Nrf2, Kelch-like ECH-associated protein 1 (Keap1), and heme oxygenase-1 (HO-1)—and inflammatory mediators—including NLRP3, IL-10, interleukin-18 (IL-18), and IL-1β—will be assessed via Western blot analysis. Concurrently, the mRNA expression levels of HO-1 will be quantified using RT-qPCR, and relative gene expression will be calculated using the 2^−ΔΔCt^ method. Detailed protocols for the measurement of intracellular ROS levels, protein extraction, Western blot analysis, RNA extraction, and RT-qPCR are provided in the **Supplementary Material**.

#### EPC culture under human serum conditions and cellular analyses

2.13.10

To further investigate whether exercise confers endothelial protection by modulating EPC function, EPC-related analyses will be conducted using peripheral blood samples collected from all participants in both the AE and CON groups. EPCs will be cultured and maintained within a human serum–based system using serum obtained from the same participants at the corresponding time points, aiming to more closely mimic the *in vivo* circulating microenvironment while preserving inter-individual biological variability.

Anticoagulated peripheral blood samples will be diluted with phosphate-buffered saline (PBS), and peripheral blood mononuclear cells (PBMCs) will be isolated via density gradient centrifugation. The isolated cells will then be seeded onto fibronectin-coated culture plates and maintained at 37 °C in a humidified incubator with 5% CO_2_. The culture medium will consist of endothelial basal medium supplemented with 5% autologous human serum, without the addition of fetal bovine serum (FBS). Endothelial colony-forming units (CFU-EC/CFU-Hill colonies) will be identified and quantified between days 7 and 10 of culture as a functional index. These colonies will be identified based on their characteristic morphology, consisting of a central cluster of rounded cells surrounded by radiating spindle-shaped cells. For subsequent molecular analyses, the adherent EPCs derived from these colonies will be expanded. Upon reaching 80%–90% confluency, these cells will be subcultured, with early passages (P1 to P3) used to evaluate redox homeostasis and inflammatory markers. The molecular biomarkers to be evaluated in EPCs will be consistent with those assessed in the HUVEC experiments.

### Statistical analysis

2.14

All statistical analyses will be conducted using R (version 4.3.1; R Foundation for Statistical Computing, Vienna, Austria). For descriptive statistics of baseline characteristics, normally distributed continuous variables will be expressed as 
mean±standard deviation (SD), whereas non-normally distributed data will be presented as median (interquartile range [IQR]). Categorical variables will be expressed as frequencies and percentages [n (%)]. Intergroup comparisons of baseline characteristics will be performed using independent t-test or Mann–Whitney U test for continuous data, and Chi-square (χ^2^) or Fisher’s exact test for categorical data, as appropriate. Efficacy analyses will follow the intention-to-treat (ITT) principle, including all randomized participants. To evaluate intervention effects between baseline and week 12, a linear mixed-effects model (LMM) will be employed. In this model, time (baseline and week 12), group (AE vs. CON), and the 
group×time interaction term will be included as fixed effects, while participants will be treated as a random effect (random intercept) to account for the intra-individual correlation arising from repeated measurements. Primary inferences will be based on the 
group×time interaction term to determine whether the change over time differs significantly between the two groups. If the interaction term reaches statistical significance, further *post hoc* comparisons will be performed to examine intergroup differences at week 12 and intragroup changes from baseline to week 12. Model estimates will report estimated marginal means with their corresponding 95% confidence intervals (CIs). Since LMMs provide unbiased estimates under the missing at random (MAR) assumption by utilizing all available data, no additional data deletion will be performed. As a sensitivity analysis, a per-protocol (PP) analysis will be conducted, including only participants who completed ≥ 75% of the prescribed training sessions and had no major protocol deviations. Furthermore, sensitivity analyses for all outcome measures will be further adjusted for potential confounders, such as age and sex, to verify the robustness of the findings. The primary outcome will be used for confirmatory inference. Secondary outcomes will be considered exploratory, and no formal adjustment for multiple comparisons will be applied; therefore, these results will be interpreted with caution, with emphasis on effect sizes and consistency of findings. All statistical tests will be two-sided, and *P* < 0.05 will be considered statistically significant.

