### Inclusion criteria

2.3

Participants must meet all of the following criteria: (1) diagnosis of IGT, specifically defined as: a 2-h postload plasma glucose (2-h PG) level ≥ 7.8 mmol/L and < 11.1 mmol/L as confirmed by a 75-g oral glucose tolerance test (OGTT), with a fasting plasma glucose (FPG) level < 7.0 mmol/L (17); (2) age between 45 and 65 years; (3) identified as a “low physical activity level” via the International Physical Activity Questionnaire (IPAQ), with no regular exercise history; (4) normal cognitive function and the physical capacity necessary to complete the exercise intervention and clinical assessments; and (5) voluntary participation in the study with signed written informed consent.

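### The random-intercept model by default gives both visits and both arms one variance, so the AE week-12 and AE change intervals can be too narrow; the confirmatory FMD test is almost untouched

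*Protocol article*

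**What the plan says.** Section 2.14 (Statistical analysis) specifies a linear mixed model with time, group and their interaction as fixed effects. On the covariance it says only that "participants will be treated as a random effect (random intercept) to account for the intra-individual correlation arising from repeated measurements". It names no variance function by visit or arm.

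The primary inference rests on the "interaction term to determine whether the change over time differs significantly between the two groups". If that term is significant, further "comparisons will be performed to examine intergroup differences at week 12 and intragroup changes from baseline to week 12". Separately, and not tied to significance, "Model estimates will report estimated marginal means with their corresponding 95% confidence intervals (CIs". On missing data the section relies on the model: "Since LMMs provide unbiased estimates under the missing at random (MAR) assumption by utilizing all available data".

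On the status of the outcomes: "The primary outcome will be used for confirmatory inference", and "Secondary outcomes will be considered exploratory, and no formal adjustment for multiple comparisons will be applied".

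Section 2.3 (Inclusion criteria) requires a 2-h glucose of at least 7.8 and below 11.1 mmol/L, "as confirmed by a 75-g oral glucose tolerance test (OGTT". Section 2.5 gives a pooled SD of 2.2 for FMD. No SD by visit or arm, and no between-visit correlation, is given anywhere.

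**The concern.** With two visits, a participant random intercept plus a single residual variance is compound symmetry: one total variance and one correlation for everyone. Two features of this trial make that doubtful.

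- Only the AE arm trains. If people respond to training to different degrees, variance is added in AE at week 12 and nowhere else.
- Entry restricts 2-h glucose to a band 3.3 mmol/L wide. Week 12 has no such restriction.

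The model then builds the standard error of each marginal mean, of each within-group change and of the week-12 contrast from averaged variances. Where the true spread is above the average the interval is too narrow, and where it is below, too wide. These intervals will be read closely, because 2.14 asks that secondary outcomes be judged on effect sizes and consistency rather than on adjusted tests.

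**Working it through.** **The plan's own figure.** From 2.5: δ = 1.77, σ = 2.2, two-sided α = 0.05, power 85%. n per group = 2(1.960 + 1.036)² × 2.2² / 1.77² = 27.7, so 28; total 56; 56/0.8 = 70. The stated figures reproduce (normal approximation).

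**Inputs for the check.** 35 per arm and σ = 2.2 come from 2.5. The rest is assumed: 2.2 is the SD at each visit without training response, the visit correlation is 0.6, and individual response has SD τ = 1.5 or 2.0 points, independent of the rest and in AE only.

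**Formulas (complete data, equal arms, large sample).** The model's total variance v is the mean of the four arm-by-visit variances. Its change variance is the mean of the two arms' change variances. Coverage of a nominal 95% interval = 2Φ(1.96 × √(model variance / true variance)) − 1.

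Visit variance without response: 2.2² = 4.84. Change variance in CON: 2 × 4.84 × (1 − 0.6) = 3.872.

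| Quantity | τ = 1.5 | τ = 2.0 |
|---|---|---|
| AE week-12 variance, 4.84 + τ² | 7.09 | 8.84 |
| v = (3 × 4.84 + AE week-12) / 4 | 5.4025 | 5.84 |
| AE week-12 mean: v / true | 0.762, coverage 91.3% | 0.661, coverage 88.9% |
| Week-12 difference: 2v / (4.84 + AE week-12) | 0.906, coverage 93.8% | 0.854, coverage 93.0% |
| AE change variance, 3.872 + τ² | 6.122 | 7.872 |
| Model change variance (mean of arms) | 4.997 | 5.872 |
| AE change: model / true | 0.816, coverage 92.3% | 0.746, coverage 91.0% |

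Simulation with fitted random-intercept REML models (35 per arm, same assumptions, with and without dropout) agrees: 88–92% for the AE week-12 mean and 89–92% for the AE change, against about 95% with no response heterogeneity.

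**If spread shrinks.** With the AE week-12 SD at 0.67 of baseline and the other three cells unchanged, large-sample coverage is 99.3% for the AE week-12 mean and 96.8% for the week-12 difference, so the intervals are too wide.

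**The confirmatory test.** With complete data the interaction is a two-sample t-test on change scores. With equal arms the model's variance, 2 × 4.997/35, equals the true one, (3.872 + 6.122)/35, so the test is unaffected. Simulated rejection of a true null is 4.7–5.7% with complete data or equal dropout.

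With about 30% AE and 10% CON dropout there are 24 and 32 completers. An approximation from completers only:

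- τ = 1.5: pooled change variance (23 × 6.122 + 31 × 3.872)/54 = 4.830. Model: 4.830 × (1/24 + 1/32) = 0.352. True: 6.122/24 + 3.872/32 = 0.376. Ratio 0.937, type I error 5.8%.
- τ = 2.0: pooled 5.576. Model 0.407, true 0.449. Ratio 0.905, type I error 6.2%.

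Mixed-model simulations with a t reference at 11/3 or a similar imbalance gave 5.2–7.0%.

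**2-h glucose.** A uniform spread over the entry band has SD 3.3/√12 = 0.95. Suppose the qualifying OGTT is reused as baseline (SD about 0.9) and the week-12 SD is 1.5 to 2.0 in both arms. Then v = (0.81 + 2.25)/2 = 1.53 or (0.81 + 4)/2 = 2.405. The ratios to the true week-12 variance are 0.680 and 0.601, and the week-12 contrast tested alone rejects a true null in 10.6–12.9%. The plan, however, runs that contrast only after a significant interaction. In simulation the interaction rejects in 4.7–5.3%, and both reject in only 3.3–3.8%. With a fresh OGTT at day 0, even the ungated contrast is at 4.3–5.4%.

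**The case against.** The strongest reply is that this does not reach the trial's conclusion. FMD is the only confirmatory outcome, its inference is the interaction, and at 1:1 allocation that test tolerates unequal variances. This stands. A reader might infer that the primary test is invalid. The documents do not support that: 2.5 plans 20% dropout and states no imbalance, and even at 30% against 10% the excess is one or two points and needs a response SD close to or above the whole planned effect of 1.77.

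A reader might also infer false week-12 claims on 2-h glucose in more than one trial in ten. That reading ignores the gate on a significant interaction and assumes the qualifying OGTT is reused. Table 1 places eligibility screening and the baseline glucose assessment in separate columns and does not say the screening value is carried forward. The entry criteria restrict only fasting and 2-h glucose, both exploratory, and not FMD.

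A further tempting step is to call the missing-at-random statement wrong. How the model borrows from baseline does depend on the covariance, but no size of bias has been worked out and none is claimed here.

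Lastly, a random intercept does not exclude a residual variance function, which an analysis plan not shown could add. True, so the text imposes equal variances by default rather than by necessity. But 2.14 does state the covariance model, and a reader following it would fit the common-variance version. The marginal means and their intervals are reported whether or not the interaction is significant, so the gate does not protect them.

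**Conclusion.** The point holds for the reported intervals and not for the primary conclusion. Under assumed individual-response SDs of 1.5–2.0 FMD points, nominal 95% intervals for the AE week-12 mean and the AE within-group change cover about 88–92%, and the week-12 difference about 93–94% with complete data. If training narrows the spread, the error runs the other way. The direction and size are unknown because the documents give no SD by visit or arm.

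The confirmatory group×time test is essentially at its nominal level, rising to about 5–7% only when heterogeneous response and markedly unequal dropout occur together. A false week-12 claim on 2-h glucose stays below 5% under the planned gate, and the restricted range matters at all only if the screening OGTT doubles as baseline. This is a worthwhile, low-cost improvement of the method, not a threat to the trial's main inference.

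**What to change.** In 2.14, replace the random intercept with a two-visit covariance that lets the variance differ by visit and arm, and name which form is used:

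- a mixed model for repeated measures with an unstructured covariance estimated separately in each arm: six covariance parameters against two under the present model, so four extra; or
- generalised least squares in R with variances by arm × visit (`varIdent`) and one correlation common to both arms: five parameters, so three extra.

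The two are not the same model, because the second shares the correlation between arms. State small-sample degrees of freedom, and apply the choice to FMD and to the secondary outcomes.

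The cost is one sentence in the analysis section and a small change of code, with no new data and no change in sample size. The downside is a negligible loss of precision if the variances are in fact equal. Recruitment is still under way, so the change can be made before unblinding.

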## Discussion

3

Individuals with IGT, representing an early stage in the progression of metabolic diseases, are a critical target for intervention. AE is recognized as a cornerstone lifestyle intervention capable of enhancing metabolic function. While extensive research has established that AE significantly mitigates the risk of IGT progressing to T2DM, evidence regarding its efficacy in improving specific glycemic parameters in patients with IGT remains inconsistent (22, 23). To address this, the present study will systematically evaluate the potential effects of AE on the glycemic status of patients with IGT by assessing FBG, 2-h PPG, HbA1c, OGTT performance, and insulin resistance levels. Furthermore, central obesity—characterized by abdominal adipose accumulation—is intricately linked to the metabolic disturbances and cardiovascular risks associated with IGT (24, 25). Therefore, this study will also employ waist-to-hip ratio (WHR) measurements, bioelectrical impedance analysis, and ultrasound imaging to assess abdominal fat distribution, allowing for a deeper exploration of the impact of AE on central obesity and regional fat deposition in the IGT population.

Beyond metabolic impacts, vascular structural and functional impairments represent critical pathological features of IGT. Previous research indicates that individuals with IGT already exhibit a discernible predisposition toward atherosclerosis, with endothelial dysfunction recognized as a pivotal early event in this process (26, 27). Nevertheless, clinical evidence regarding the influence of AE on the atherosclerotic process specifically in patients with IGT remains relatively limited. Consequently, the present study will employ FMD and baPWV to assess the impact of AE on vascular endothelial function and the severity of arterial stiffness in this population.

Oxidative stress and inflammation are recognized as fundamental mechanisms driving IGT-associated endothelial dysfunction and the development of atherosclerosis (7, 28). However, due to the inherent challenges in directly obtaining vascular endothelial tissue from patients in a clinical setting, empirical evidence regarding whether AE-mediated endothelial protection is achieved through the modulation of oxidative stress and inflammatory responses remains scarce. The exercise-conditioned serum technique—which involves applying human serum collected before and after an exercise intervention to cell cultures—enables the observation of how exercise-associated circulating factors regulate cellular phenotypes and signaling pathways. This approach has been widely implemented in exercise-related endothelial biology research (15). Furthermore, as precursors to endothelial cells, EPCs play a crucial role in reflecting vascular repair capacity and endothelial function; notably, individuals with IGT frequently exhibit impaired EPC mobilization and functional deficits (29). Building on this rationale, the present study will integrate exercise-conditioned serum experiments with *in vitro* EPC analysis. HUVECs will be treated with serum collected from IGT patients before and after the intervention, while EPC-related markers will be evaluated in parallel. The effects of AE on endothelial oxidative stress will be assessed by measuring intracellular ROS levels and antioxidant-related markers, including Nrf2, and HO-1. Inflammatory responses will be evaluated by quantifying pro-inflammatory mediators (NLRP3, IL-18, and IL-1β) and the anti-inflammatory cytokine IL-10. Moreover, given the systemic impact of oxidative stress and inflammatory responses on metabolic and vascular health, this study will also quantitatively assess circulating biomarkers of oxidative stress (SOD, Nrf2, ROS, and MDA) and inflammation (NLRP3, TNF-α, IL-6, IL-10, hs-CRP, and IL-1β). This approach will provide a comprehensive evaluation of how AE modulates the redox status and inflammatory profile in the IGT population.

Consequently, this study will focus on the dual pathological hallmarks of oxidative stress and inflammation. By evaluating endothelial function in conjunction with two distinct experimental paradigms—exercise-conditioned serum and EPC analysis—we will seek to conduct an in-depth investigation into the potential mechanisms underlying AE-mediated endothelial protection. This research is designed to bridge the existing gap between basic physiological mechanisms and organ-scale functional performance. By integrating clinical evidence with a multidimensional mechanistic exploration spanning the “molecule-cell-organ” hierarchy, this study will provide novel insights and a theoretical basis for exercise prescriptions tailored to patients with IGT.

